## Protocol amendments (Version 2 to Version 3)

| Previous protocol               | New protocol                    |
|---------------------------------|---------------------------------|
| Version 2
Date: 18 June 2020 | Version 3
Date: 28 July 2020 |

| Inclusion criteria                                                                                                                                                                                                                                                                                                                                                                                                                                                                                                                                                                                                                                                                                                                                                                                                                                                                                                                                                                                                                                                                                                                                                                                                                                                                                                                                                                                                                                                                                                                                                                                                                                                                                                                                                                                                                                                                                                                                                                             |
|------------------------------------------------------------------------------------------------------------------------------------------------------------------------------------------------------------------------------------------------------------------------------------------------------------------------------------------------------------------------------------------------------------------------------------------------------------------------------------------------------------------------------------------------------------------------------------------------------------------------------------------------------------------------------------------------------------------------------------------------------------------------------------------------------------------------------------------------------------------------------------------------------------------------------------------------------------------------------------------------------------------------------------------------------------------------------------------------------------------------------------------------------------------------------------------------------------------------------------------------------------------------------------------------------------------------------------------------------------------------------------------------------------------------------------------------------------------------------------------------------------------------------------------------------------------------------------------------------------------------------------------------------------------------------------------------------------------------------------------------------------------------------------------------------------------------------------------------------------------------------------------------------------------------------------------------------------------------------------------------|
| Version 2
Not applicable                                                                                                                                                                                                                                                                                                                                                                                                                                                                                                                                                                                                                                                                                                                                                                                                                                                                                                                                                                                                                                                                                                                                                                                                                                                                                                                                                                                                                                                                                                                                                                                                                                                                                                                                                                                                                                                                                                                                                             |
| Version 3
Addition
COVID-19 symptom onset of less than 8 days with the day of onset of symptoms counted as Day 0                                                                                                                                                                                                                                                                                                                                                                                                                                                                                                                                                                                                                                                                                                                                                                                                                                                                                                                                                                                                                                                                                                                                                                                                                                                                                                                                                                                                                                                                                                                                                                                                                                                                                                                                                                                                                                                           |
| Reason

This is in response to the CTC discussion and written recommendation dated 27 July 2020 to only include participants with early disease.
 
The population who may benefit from early antiviral therapy are those who are ambulatory but may progress to requiring hospitalisation while in self-isolation. This population is likely to include individuals with underlying co-morbidities as outlined in our inclusion criteria. However, we feel that it is still important to include a smaller group of low-risk participants in our study to learn more about natural history. Treatment as early as possible after symptom onset is likely an important predictor of an antiviral efficacy to prevent disease progression. The more difficult assessment is when antiviral therapy is too late, most likely when the inflammatory components of COVID-19 disease predominate. We made the following assumptions:
 
 
• Our primary endpoint is the development of lower respiratory tract symptoms defined as SpO2<93% or decline from baseline of 6% in 2 measurements at least 2 hours apart. We assume that our participant population will deteriorate based on their co-morbidities and risk factor profile and reviewed when viral burden is expected to reach maximum levels in a hospitalised population.
 
• The highest detection of SARS-CoV-2 RNA in serum and throat samples are between 11 to 15 days after symptom onset in hospitalised patients. Others also support that viral load shedding peaks around 15 days in hospitalised patients.
 
• We conservatively took 11 days as the viral peak and concluded that at minimum, a 5 day course should be administered prior to the viral peak based on oseltamivir experience for influenza. Therefore the last day of treatment initiation after symptom onset should be day 7.
 
 |

- Initiating treatment from day 7 onwards for 5 days will take us to day 11 from symptom onset. We therefore set the inclusion criteria that participants should only be enrolled and initiated on antiviral therapy less than 8 days from symptom onset.

## 7.10 Additional treatment arm selection in future protocol amendments

### Version 2

Not applicable

### Version 3

#### *Addition*

The TOGETHER Consortium is a multi-site platform trial to evaluate affordable and scalable outpatient treatment options. The flexible platform trial design will allow additional agents to be added into the trial. Therefore, this will not be a randomised clinical trial solely focused on the current protocol interventions, and new interventions will be added later into the trial based on new emerging evidence. Any amendments require regulatory and ethical approval prior to implementation. The future intervention selection will be through the COVID-19 Therapeutics Accelerator initiative funded by the Bill and Melinda Gates Foundation (BMGF).

The COVID-19 Therapeutics Accelerator is supported by a multi-disciplinary group of clinicians and scientists who provide heuristic input on intervention selection based on clinical safety, clinical pharmacology and suitability for low middle-income countries; considerations such as ease of use, adherence and manufacturing and scale up all influence the selection of regimens to study. The COVID-19 Therapeutics Accelerator further examines activity of putative antivirals in various cell lines including VERO E6 cells, human lung epithelial cells, CALU-3 human lung cancer cells and others. Examination of both activities alone and also in combination therapy is under way. Therapy regimens are also guided by in silico assessments using viral cell cycle model and translational approaches including physiological based PK modelling, to contextualize the concentrations in vitro to what might be achieved in vivo.

The decision to add new interventions into the TOGETHER Consortium will be facilitated by Cytel who regularly engage with the BMGF and the COVID-19 Therapeutics Accelerator. With funding from the BMGF, Cytel has created a real-time global COVID-19 clinical trial tracker ([www.covid19-trials.org](http://www.covid19-trials.org)) to collate all clinical trials registered across several global clinical trial registries. For the TOGETHER Consortium, this trial tracker will collate all clinical trials related to COVID-19 in order to capture rapidly emerging scientific evidence on clinical trial results and new interventions in a timely manner. If relevant scientific evidence emerges on new therapies, the global trial tracker will allow for rapid assessment to allow for new therapies to be added into the TOGETHER Consortium in a timely manner.

In the TOGETHER Consortium, an independent DSMB as well as the international investigators will continuously review the release of data on COVID-19 treatment interventions that can be delivered in outpatient setting. At the discretion of the independent DSMB, interim assessment of interventions may be triggered at any time or during the monthly meetings to assess safety and futility. Interim futility assessment will be done using Cytel's Bayesian predictive power method where a posterior predictive probability of rejecting the null hypothesis at the final analysis will be assessed given the interim data observed at analysis. Data demonstrating futility will lead to the discontinuation of treatment arms with the replacement of other investigational arms. The data from the 3 countries will be combined to rapidly provide efficacy and safety data of interventions and complete trials from each country will not necessarily be required.

In order to detect important treatment effects that are generalizable to subgroups or the larger population, we require large sample sizes representing the subgroups and different geographies. A strategy to overcome the generalizability challenges of individual clinical trials is to test the treatments among different populations in different geographies. In the TOGETHER 1 (US), 2 (Brazil) trials, each setting will test the efficacy, safety and utility of lopinavir-ritonavir in the different geographies taking into account the broad populations as well as subgroups that include sex, disease status, age, co-morbid conditions, race, etc. This will allow the combined analysis to determine whether this intervention can be provided to the broad populations or specific subgroups, as opposed to only detecting effects among specific subgroups in one geographic location, that may indicate type 2 error.

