A blinded sample size re-assessment will be done to potentially increase the sample size target during the trial, should a lower control event rate (CER) and/or higher drop-out rate be observed. The decision on the timing of the sample size re-assessment will be made by the independent DSMB during the trial based on the observed recruitment rate. The DSMB will also decide on a possible interim analysis during the trial after the sample size re-assessment based on the information on the observed recruitment rate, the CER, the drop-out rate, and the final sample size target, if applicable.

The decision for interim analysis will be made in a blinded manner (e.g., based on pooled number of events). The interim monitoring plan (written by the Study Statistician) will define monitoring bounds to maintain the two-sided type I error rate at the desired 5% (e.g. 97.5% or higher

| Harmonized protocol document                                                          |
|---------------------------------------------------------------------------------------|
| Short title: Outpatient Management of SARS-CoV-2 for High-Risk Adults in LMICs |

probability of superiority over the control group). Should a new experimental candidate be added during the trial, allocation ratios will be adapted to favor the new arm.

If additional data emerge on alternative potentially effective agents for SARS-CoV-2, additional arms can be added to the study as a new intervention appendix to the protocol. The standardized operating procedures and comprehensive statistical analysis plans will allow for integration of new arms.

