### 7.4. ***Method of Treatment Assignment***

Participants will be randomized at an equal allocation ratio between experimental intervention and control groups at the level of the individual.

|                                          |                 |
|------------------------------------------|-----------------|
| Date/version: May 19, 2020 – V1.0 | Page: 30 |
|------------------------------------------|-----------------|

| Harmonized protocol document                                                          |
|---------------------------------------------------------------------------------------|
| Short title: Outpatient Management of SARS-CoV-2 for High-Risk Adults in LMICs |

The randomization plan will be overseen by the Study Statistician. The randomization code and resulting allocation list will be generated and overseen by the Study Statistician. The list will be blocked and stratified by site and risk level.

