## **12. Statistical Considerations**

### **12.1. Sample Size Determination for Brazil**

The sample size for Brazil of 492 patients per arm has been chosen for each experimental group to achieve 90% power with 0.05 two-sided Type 1 error for a pairwise comparison against the control (ascorbic acid) to detect minimum treatment efficacy defined by 27.5 % relative risk reduction (RRR) of preventing hospitalization assuming a control event rate (CER) of 20%.

The table below shows the sample size required at various treatment effects, CER, and drop-out rates for operating characteristics of 90% statistical power and two-sided type I error rate of 5%. Power may be lower depending on CER and drop-out rate (Table 1). As the initial sample size target, 165 per arm has been initially chosen for each experimental group to achieve 90% power with 0.05 two-sided Type 1 error for a pairwise comparison against the control (ascorbic acid) to detect at least 50% treatment efficacy in reducing the progression to LRTI (primary endpoint) assuming a CER of 30% and 5% drop-out rate.

**Table 1 Sample Size Per Arm Required to Detect a Relative Risk Reduction of 40% to 60% Under Various Control Event and Drop-out Rates**

| RR
R | Drop-out rate = 0% |             |             | Drop-out rate = 5% |             |             | Drop-out rate = 20% |             |             |
|---------|--------------------|-------------|-------------|--------------------|-------------|-------------|---------------------|-------------|-------------|
|         | CER=1
0%        | CER=2
0% | CER=3
0% | CER=1
0%        | CER=2
0% | CER=3
0% | CER=1
0%         | CER=2
0% | CER=3
0% |
| 40
% | 962                | 437         | 261         | 1013               | 460         | 275         | 1202                | 546         | 327         |
| 50
% | 578                | 263         | 158         | 609                | 277         | 165  | 723                 | 329         | 198         |
| 60
% | 375                | 171         | 103         | 395                | 180         | 108         | 469                 | 214         | 128         |

**Acronyms:** CER: Control event rate; RRR: Relative risk reduction.

Sample size calculation was done with the desired operating characteristics of 90% statistical power and 5% type I error rate (two-sided).

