#### **Interim Analysis:**

The DSMB will decide on a possible interim analysis during the trial after the sample size re-assessment based on the information on the observed recruitment rate, the CER, the drop-out rate, and the final sample size target, if applicable. The decision for interim analysis will be made in a blinded manner (e.g., based on pooled number of events). The interim monitoring plan (written by the Study Statistician) will define monitoring bounds to maintain the two-sided type I error rate at the desired 5% (e.g. 97.5% or higher probability of superiority over the control group). Should new experimental candidates be added during the trial, allocation ratios will be adapted to favor the new arms.

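### Section 7.10 allows futility assessments at any time, which does not fit the single blinded interim in 5.1 and 12.3.1, and the power in 12.1 makes no allowance for futility stopping

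*Protocol*

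**What the plan says.** Section 7.10 (Additional treatment arm selection in future protocol amendments) is text that Version 3 adds. It provides that "interim assessment of interventions may be triggered at any time or during the monthly meetings to assess safety and futility". The futility tool is the predictive probability of rejecting the null hypothesis at the final analysis, given the interim data. The consequence follows directly: "Data demonstrating futility will lead to the discontinuation of treatment arms with the replacement of other investigational arms".

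Section 5.1 describes something narrower: "The DSMB will also decide on a possible interim analysis during the trial after the sample size re-assessment". Section 12.3.1, under Interim Analysis, repeats this and adds: "The decision for interim analysis will be made in a blinded manner (e.g., based on pooled number of events"). Both sections tie the interim monitoring plan to bounds that hold the two-sided type I error at 5%. Section 5.1 lists operational futility, social harms and efficacy as the DSMB's purpose.

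In section 12.1, "492 patients per arm has been chosen for each experimental group to achieve 90% power with 0.05 two-sided Type 1 error", for a 27.5% relative risk reduction in hospitalization from a control rate of 20%. Futility stopping is not mentioned there. Section 12.3 says that an Interim Monitoring Plan will be developed.

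**The concern.** A look at any time may come before the sample size re-assessment, and monthly looks are not one possible interim. Nothing in the protocol says which rule governs, or that the two rules concern different analyses. A DSMB following 7.10 could act outside what 5.1 and 12.3.1 describe.

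The stake is type II error. Each binding futility look adds a chance of dropping an arm that would have succeeded at the end, and early looks carry the least information. The power in 12.1 is then not the power of the design as it would be run. Predictive probability is also defined against the final analysis, so its value depends on the final size assumed, and the protocol gives more than one: 492 per arm (synopsis, 5.1, 12.1) and 165 per arm as an initial target (sections 3, 5.2, 12.1) that 5.2 expects to increase.

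**Working it through.** **Inputs from the protocol.** Two-sided alpha 0.05, 90% power, 492 per arm, control rate 20%, relative risk reduction 27.5% (12.1), so the treated rate is 0.20 × (1 − 0.275) = 14.5%. Equal allocation (7.4). Not given: futility cut-off, prior, number of looks, minimum information.

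**1. The plan's own figures.** Table 1 follows the fixed-sample formula with unpooled variance:

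n = (1.960 + 1.282)² × [p₁(1−p₁) + p₂(1−p₂)] / (p₁−p₂)²

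- 10% vs 6%: 961.4, so 962 (Table 1: 962).
- 20% vs 10%: 262.7, so 263 (Table 1: 263).
- 30% vs 15%: 157.6, so 158 (Table 1: 158). With 5% drop-out, 157.6/0.95 = 165.9 (stated: 165).

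The formula has no term for interim stopping.

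**2. The 492.** For 20% vs 14.5% the same formula gives (3.242)² × (0.1600 + 0.1240)/0.055² = 986.4, so 987 per arm, not 492. At 492 per arm the standardized effect is 0.055/√(0.2840/492) = 2.29, and power is Φ(2.29 − 1.96), about 63%. The stated 90% is therefore not reached even without a futility rule.

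**3. Cost of futility looks.** At information fraction t, the flat-prior predictive power is

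PP = Φ[(z/√t − 1.96) / √((1−t)/t)]

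The arm stops if PP is below the cut-off, and success at the end requires z > 1.96. The test statistic is simulated with drift 3.242, that is, a true 90% design of about 987 per arm. Assumed schedules: 8 equally spaced futility looks before the final analysis, or one look at t = 0.5. Every look is applied and is binding.

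| Cut-off | Power, 8 looks | Points lost, 8 looks | Points lost, one look at half |
|---|---|---|---|
| 1% | 89.4% | 0.6 | 0.1 |
| 5% | 86.4% | 3.6 | 0.5 |
| 10% | 82.5% | 7.5 | 1.2 |
| 20% | 74.4% | 16 | 3.0 |

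If the 8-look schedule is kept but nothing is tested before half information, a 5% cut-off costs about 1 point. At 492 per arm, 8 looks take the 63% to about 59%, 54% and 47% at cut-offs of 5%, 10% and 20%.

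**4. Dependence on the final size.** Suppose 120 per arm have outcomes, at 20% vs 14.5%. Then z = 0.055/√(0.2840/120) = 1.13.

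- Against 165 per arm: t = 0.727, PP = Φ[(1.326 − 1.960)/0.612] = Φ(−1.04), about 15%.
- Against 492 per arm: t = 0.244, PP = Φ[(2.289 − 1.960)/1.761] = Φ(0.19), about 57%.

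At a 20% cut-off, the same data stop the arm under one size and continue it under the other.

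**The case against.** **The power loss is not in the document.** A reader might infer that 7.10 takes several points off the stated power. The protocol does not support that as an unconditional claim. Assessments may be triggered; they are not scheduled. The cut-off, prior and look schedule are ordinary content of the Interim Monitoring Plan, which is not shown. With a 1% cut-off, or with no look before half information, the loss is about a point or less. A prior centred nearer the design effect would also soften early looks. This stands. What remains is the direction of the effect and the absence of any allowance for it in 12.1.

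**The sections may concern different analyses.** The bounds in 5.1 and 12.3.1 protect type I error, which suggests an efficacy interim, while 7.10 speaks of safety and futility. The reading is possible, but no section states it, and 5.1 gives the DSMB only operational futility. A later monitoring plan can supply parameters; it cannot make two protocol rules agree.

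**Blinding.** A reader might infer that 7.10 permits looks timed on by-arm results. It says nothing on this. Sections 5.1 and 12.3.1 blind only the decision to hold an interim, and 7.10 omits that safeguard without expressly contradicting it.

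**How often an effective arm would stop.** At 492 per arm, a count of stopped arms would overstate the harm, because about 37% of such trials fail without any futility rule and most stopped arms come from that group. Lost power is the right measure.

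**Status of 7.10.** It appears among the amendments, and body section 7 ends at 7.9. But it is the wording that Version 3 adds, not superseded text, so it has to fit the body.

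**Conclusion.** The point holds as a conflict between current provisions plus a gap in the power statement. Section 7.10 permits futility assessments at times that 5.1 and 12.3.1 do not foresee, omits their blinded-decision safeguard, and words discontinuation as automatic. The power in 12.1 comes from a calculation without futility stopping.

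The size is conditional. With 8 looks and a flat prior, the loss runs from about 0.6 to 16 points over cut-offs of 1% to 20%; with one look at half information, from about 0.1 to 3. All of this assumes a binding rule applied at every look. Type I error is not at issue, since futility stopping does not raise it.

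Two related facts do not depend on those assumptions. At 492 per arm, power for the stated effect is about 63%, a separate shortfall of 27 points that exceeds every loss in the table. And predictive probability has no single meaning until the final size is named. The 165 target was derived for the LRTI endpoint, so the 15% versus 57% contrast illustrates the ambiguity and does not predict a decision.

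**What to change.** - Reconcile 7.10 with 5.1 and 12.3.1, and state whether they govern the same or different analyses.
- Keep safety review possible at any time.
- Limit futility testing to looks set in advance by pooled primary-outcome information, with a stated minimum information fraction, and carry over the blinded decision to hold a look.
- Compute predictive probability against one named final size, and state or cross-refer to the cut-off and prior.
- Say whether the futility rule is binding or advisory.
- Restate the power in 12.1 from the correct baseline, with the futility rule included.

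The cost is wording in four sections and one simulation. The downside is that a futile arm may run somewhat longer and the stated power will be lower. Correcting the baseline also brings the separate 492-per-arm shortfall into the open, and that may need its own decision on sample size.
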